### Use of a Team Science Approach

Replication issues in psychological science have been well documented [42,43], motivating efforts to address them at the study design stage, including efforts to increase both the size and representativeness of the samples under study [44,45]. One strategy for achieving this goal is to conduct team science, defined as a “method involving a relatively large number of collaborators who may be dispersed across labs, institutions, disciplines, cultures, and continents” [46]. The goal is to facilitate replicable research by helping researchers pool their resources to reduce study burden while increasing the size and representativeness of the study sample.

In accordance with this recommendation, this study was designed and proposed and will be conducted by members of the Exposure Therapy Consortium (ETC [47] ) [9]. This study responds to recommendations for team science [46] by using a consensus design (ie, examined and approved by the ETC Rigor and Reproducibility Committee and the research steering committee [9]); multiple measures for select constructs; strong documentation of materials and methods; a large and diverse sample; collaboration with colleagues from different settings, backgrounds, and cultures; registration of the trial and analytic plan; and a plan to share data and analytic codes through Open Science Framework registration. To this end, this team science approach will not only enhance the replicability of this study but also enable a more comprehensive investigation of the intricate interplay between positive affect and exposure therapy outcomes across diverse populations and settings.

## Methods

### Sites

This is a multicenter study with 12 participating sites. Boston University serves as the lead site (coordinating center), distributing study methods and materials to the collaborating investigators at Albright College, Curtin University, Erasmus University Rotterdam, Southern Illinois University, Tufts University, University of Arizona, University of Hong Kong, Marburg University, University of New South Wales, University of Texas at Austin, and Utrecht University. Adherence to study procedures is aided by videotaped procedures distributed to the sites. All data entry is conducted via self-report using a REDCap (Research Electronic Data Capture; Vanderbilt University) interface. Each site is asked to screen up to 150 participants, from whom up to 80 participants (the minimal target sample size per site is 40) are to be selected for the VR exposure intervention and posttreatment and follow-up assessments. If needed, each site is permitted to recruit beyond 150 participants for the screening phase to reach the target sample size in the intervention phase. This study is registered with ClinicalTrials.gov (NCT06593847).

### Participants

Participants for this study will be undergraduate students reporting high levels of public speaking anxiety who are willing to engage in a single-session intervention. Inclusion criteria for the screening phase of this study (see the Procedures section) are self-reported age of between 18 and 70 years, current attendance to college, ability to read the dominant language used at the university, familiarity with a keyboard and mouse or touch screen device, and willingness to provide informed consent through the REDCap interface.

### Assessments

#### Overview

Table 1 indicates the study phase in which each variable is assessed. Demographic information will be obtained using a brief questionnaire at screening, and an additional treatment history form will be used to obtain clinical information regarding mental health diagnoses and previous mental health treatment; this information will be used to characterize the sample. All outcomes are self-reported via REDCap.

**Table 1. T1:** Assessment schedule.

Measure	Screening and baseline assessment	In-person VREX^a^ visit	1-week follow-up assessment
Selection and outcome variables			
Demographics	✓		
PRCA-PA^b^	✓	✓	✓
Valence	✓	✓	✓
SPIN^c^	✓		✓
Core predictor variables			
SAM^d^		✓	
Trait positive affect	✓		
AHS^e^	✓		
LOT-R^f^	✓		
MHSES^g^	✓		
Additional measures			
RRQ^h^	✓		
SCI^i^	✓		
CAMS-R^j^	✓		
SBI^k^	✓		
Treatment history	✓		

a VREX: virtual reality exposure.

b PRCA-PS: Personal Report of Communication Apprehension, Public Speaking Subscale.

c SPIN: Social Phobia Inventory.

d SAM: Self-Assessment Manikin.

e AHS: Adult Hope Scale.

f LOT-R: Life Orientation Test–Revised.

g MHSES: Mental Health Self-Efficacy Scale.

h RRQ: Ruminative Response Questionnaire.

i SCI: Sleep Condition Indicator.

j CAMS-R: Cognitive and Affective Mindfulness Scale–Revised.

k SBI: Savoring Beliefs Inventory.

#### Selection and Outcome Variables

The Personal Report of Communication Apprehension, Public Speaking Subscale (PRCA-PS), is a 6-item self-report measure for assessing level of public speaking anxiety; item responses range from 1 (“strongly disagree”) to 5 (“strongly agree”), providing total scores that can range from 6 to 30 [48]. Scores of 18 or higher indicate high- to moderate-severity public speaking anxiety and are used to select individuals for this study at the screening and baseline assessment. In a pilot study for this trial [49], 81.3% of the screened sample responding to advertisements for a public speaking anxiety study scored 18 or higher on the PRCA-PS, consistent with high rates of social anxiety reported for student populations [37,38]. The PRCA-PS serves as the primary outcome at the 1-week follow-up assessment.

The Social Phobia Inventory is a 17-item self-report scale to assess fear, avoidance, and physiological symptoms associated with social anxiety disorder over the previous week [50]. The total score (which can range from 0 to 68) will be used as a measure of social anxiety severity, a secondary outcome variable, and will be assessed at the screening and baseline assessment and 1-week follow-up assessments.

The valence of giving speeches is rated on a scale ranging from −3 (extremely unpleasant) to +3 (extremely pleasant). This measure will be administered at the screening and baseline assessment, immediately after treatment, and at the 1-week posttreatment assessment.

#### Core Predictor Variables

The Self-Assessment Manikin uses pictures of a humanlike form to have participants rate the degree of current pleasure, emotional arousal, and dominance by selecting the figure that most represents their current affective state on each of these dimensions [51]. The pleasure rating (ranging from 1 to 9) will be used as the measure of state positive affect, administered before and after the affect induction. In regression equations, prediction will also be examined for degree of state affective arousal.

Trait positive affect will be assessed at the screening and baseline assessment with the 4 items used by Taylor et al [23] drawn from the extraversion domain of the NEO-FFI (laughs easily, cheerful, and vivacious; reverse items: not cheerful or lighthearted and not a cheerful optimist) [24]. The total of these items rated on a 5-point Likert scale (with scores ranging from 0 to 16) will be used as a predictor of VR exposure outcome.

The Adult Hope Scale is a 12-item measure that assesses hope, a positive motivational resource consisting of agency, or goal-directed energy, and the capacity to identify pathways toward goals [52]. The total score (which can range from 8 to 64) will be used as a predictor of VR exposure outcomes.

The Life Orientation Test–Revised is a 6-item (with 4 additional filler items) measure of optimism: the dispositional tendency to expect positive outcomes of events [53]. The total score, which can range from 0 to 24, will be used as a predictor of VR exposure outcome.

The Mental Health Self-Efficacy Scale is a 7-item measure of self-efficacy for engaging in mental health–promoting behaviors, including the ability to accept uncomfortable mental events, emotions, or sensations; refrain from maladaptive coping or protective actions; and engage in health-promoting behaviors and valued activities ([name], unpublished data, April 2025). The mean confidence rating for these items (expressed as between 0% and 100% confidence in the ability to engage in these behaviors) will serve as the self-efficacy measure for predicting VR exposure outcomes.

#### Additional Measures

The following measures, used to assess degree of rumination, sleep disruption, mindfulness, and savoring, will be assessed at baseline and used in independent, exploratory analyses of associations with VR exposure treatment outcomes given findings indicating such associations [54-57]: the Ruminative Response Questionnaire, a 22-item measure assessing an individual’s tendency to ruminate when feeling sad, down, or depressed [58]; the Sleep Condition Indicator (SCI), an 8-item measure designed to assess an individual’s sleep quality over the previous month [59]; the Cognitive and Affective Mindfulness Scale–Revised, a 10-item unidimensional scale that assesses mindfulness as it is experienced in general daily occurrences [60]; and the Savoring Beliefs Inventory, a 24-item scale that assesses the tendency to savor, or amplify, positive emotions [61].

### Procedures

Select aspects of study procedures may vary from site to site (eg, follow-up session completed in person vs remotely); however, all core procedures (ie, affect induction, VR exposure, and self-report measures) remain consistent. To promote standardization of procedures across sites, study personnel were trained using an instructional video and followed a scripted protocol when implementing VR exposure; sites were also asked to track any deviations. This clinical trial is registered on both ClinicalTrials.gov (NCT06593847) and the Open Science Framework (4ucmj). No changes to the protocol, interim analyses, specific stopping rules, or external monitoring other than by the institutional review boards (IRBs) or health research ethics committees (HRECs) are planned for this study.

### Ethical Considerations

All collaborating sites received IRB or HREC approval before data collection. IRB or ethics committee approval numbers were as follows: Boston University (7565E) for which Albright College, the University of Texas at Austin, and Southern Illinois University were reliant upon; Curtin University (HRE2025-0016); Erasmus University (ETH2425-0422); Tufts University (STUDY00005259); University of New South Wales (iRECS 7416); University of Hong Kong (EA240580); University of Marburg (2024-81k); University of Arizona (STUDY00004970); and Utrecht University (FETC 25-0150). All sites provided participants with compensation through either course credits, extra credit, and or monetary compensation.

### Screening and Baseline Procedures

Interested participants responding to an advertisement for a “Virtual Reality Intervention for Speech Anxiety Study” will be given access to an online survey via REDCap [62]. Participants will be provided with an electronic consent form explaining all study procedures. If they agree to participate, they will click a button indicating their consent and will be told to continue to the screening and baseline survey. On the basis of responses to the survey (including fully completing core measures, responding correctly to quality assurance items, and completing the survey within 5 days of initiating it), eligible participants meeting the PRCA-PS selection score (>18) will be invited to the in-person session.

### In-Person Study Session

The in-person study session lasts approximately 75 minutes and begins with an orientation to the VR device. Participants will put on the headset while sitting in a chair. Participants will be oriented to the VR environment by briefly viewing a 360-degree nature scene. Following VR orientation, participants will be asked to rate their current affect and will then watch 1 of 2 short film clips (totaling approximately 5 minutes) for either positive or negative affect induction, determined via random block assignment (1:1 allocation) using an online tool [63], with a block size of 6 and separate blocks for individuals whose sex assigned at birth was male versus female, as programmed into REDCap. Participants are blind to hypotheses. Film clips are shown on a separate laptop or tablet screen. Film clips for positive affect induction were sourced from the movie *Wall-E* and from the television show *Whose Line Is It Anyway?* The film clips for negative affect induction were sourced from the movies *Bambi* and *The Champ*. Studies have demonstrated that each of these film clips is effective in eliciting the targeted affect [64-67]. Before viewing the film clips, participants will be provided with the following instructions: “Let yourself experience whatever emotions you have, as fully as you can. Don’t try to hold back or hold in your feelings.” Participants rerate their state affect following their randomized affect induction procedures.

Following affect induction and subsequent state affect ratings, participants will be shown a prerecorded exposure therapy instruction provided by a therapist from within the VR headset. Participants undergo 6 exposure trials wherein they give a speech to a virtual audience of 6 individuals sitting in chairs around a conference table or in a lecture hall in the 360-degree VR environments [68]. The topic for the speech is “something you’re proud of.” Following exposures, the VR therapist congratulates the participant and provides a short debriefing statement. Once they remove the headset, participants will be asked to rate their public speaking anxiety and current valence toward giving a speech.

### Follow-Up Outcome Assessment

One week following the completion of the single-session VR exposure intervention, participants will be scheduled for the 1-week follow-up assessment. This survey is expected to take approximately 15 minutes to complete. Participants will receive course credit for the portion of the study in which they participate. Spontaneously reported adverse events will be reported to site IRBs or HRECs.

### Data Sharing

Data will be analyzed and published by participating ETC investigators. Following publication of primary papers, deidentified data will be available to researchers who sign a data use agreement.

### Data Analysis

The preregistered analysis plan on the Open Science Framework provides specifics on the tests to be conducted. In general, a linear mixed modeling approach will be used for data analysis, examining the overall and unique prediction afforded by predictor variables of interest while accounting for variance across sites. Preliminary analyses will evaluate the effects of the experimental manipulation (affect induction) on state affect. Preliminary analyses will also examine the relationships among predictors, particularly in relation to the degree to which trait positive affect shares variance with the hypothesized related constructs of interest: optimism, hopefulness, and self-efficacy. Core analyses will use linear mixed models to examine the hypothesis that trait positive affect is a stronger predictor of outcomes than state positive affect (also accounting for state affective arousal). Core tests of hypotheses will also examine the shared and unique prediction of outcomes, relative to trait positive affect, of measures of optimism, hopefulness, and self-efficacy. The goal of these analyses is to identify the strongest predictors of outcomes to provide greater clarity on the role of positive affect (and associated constructs) as a potential moderator of outcome of exposure-based interventions.

To address missing data and dropouts, we will implement a multipronged approach. The primary analysis will follow intention-to-treat principles using multiple imputation by chained equations, incorporating all available baseline predictors, affect condition assignment, and site indicators in the imputation model. For sensitivity analyses, we will conduct complete case analysis to compare with imputed results.

Power analyses were conducted using the following assumptions: α of .05, power of 80%, and a mixed-effects modeling approach accounting for clustering within sites. We examined detectable effect sizes across a range of intraclass correlation coefficients (ICCs=0.01 to 0.30) to account for variability in site-level clustering that is commonly observed in multisite studies. With our planned sample sizes (40-80 participants per site across 12 sites), this study is adequately powered to detect clinically meaningful moderation effects under realistic ICC assumptions. For example, with low clustering (ICC≤0.05), this study can detect moderation effects of Cohen *d*=0.36 to 0.48, representing medium effect sizes that are clinically meaningful.

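### The imputation model, as listed, leaves out the state affect ratings used in the core trait-versus-state comparison, and the ratings taken right after exposure

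*Protocol article*

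**What the plan says.** Under Data Analysis, the protocol article states: "The primary analysis will follow intention-to-treat principles using multiple imputation by chained equations". It then lists what goes into the imputation: "incorporating all available baseline predictors, affect condition assignment, and site indicators in the imputation model". One sensitivity analysis is named: "For sensitivity analyses, we will conduct complete case analysis to compare with imputed results".

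The core models "examine the hypothesis that trait positive affect is a stronger predictor of outcomes than state positive affect", and they also account for state arousal. Under Core Predictor Variables, the SAM supplies the state measure: "The pleasure rating (ranging from 1 to 9) will be used as the measure of state positive affect, administered before and after the affect induction". Table 1 places the SAM at the in-person visit only, and trait positive affect at screening and baseline only.

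Two further points matter. Invitation to the visit depends on the baseline survey, "including fully completing core measures" (Screening and Baseline Procedures). At the end of the visit "participants will be asked to rate their public speaking anxiety and current valence toward giving a speech" (In-Person Study Session). The primary outcome is the public speaking subscale (PRCA-PS) at 1 week.

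**The concern.** An imputation model should hold at least the variables of the analysis model. If a predictor is left out, imputed outcomes are drawn as though unrelated to it, given what was included, and its slope is pulled toward zero. Here trait affect is in the list as a baseline measure. State affect is represented only through the randomised condition, which explains just part of the pleasure rating. The two sides of the core comparison are therefore treated unequally, and the imbalance favours the hypothesis under test.

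Because core baseline measures must be complete before the visit and the SAM is rated during it, missing values should fall mainly on the 1-week outcome, which is where this matters. The PRCA-PS and valence ratings taken just after exposure would say most about a missing 1-week value, and they are not named either.

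**Working it through.** The article states no figure on this point and no dropout rate, so there is nothing to reproduce. All rates and effects below are assumptions.

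**Which variables the list covers**

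| Variable | When measured | In the listed imputation model? |
|---|---|---|
| Trait positive affect | Screening and baseline | Yes |
| Affect condition, site | Known for all randomised | Yes |
| SAM pleasure and arousal | In-person visit | Not named |
| PRCA-PS and valence after exposure | In-person visit | Not named |

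**Closed form.** Let f be the share of 1-week outcomes missing, S state, T trait and C condition. Observed cases carry the full state slope. Imputed cases carry only the part of S that C conveys. With outcomes missing at random and C not in the analysis model:

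state slope estimated / true = 1 − f × Var(S | C, T) / Var(S | T)

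Assume that the induction shifts S by 1.5 within-condition SD and that the within-condition T–S correlation is 0.2.

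- Within-condition share of Var(S): 1 / (1 + 1.5²/4) = 1 / 1.5625 = 0.64
- Var(S | C, T) = 0.64 × (1 − 0.04) = 0.6144
- Var(S | T) = 1 − 0.04 × 0.64 = 0.9744
- Ratio = 0.6144 / 0.9744 = 0.6305

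| Missing | Factor, shift 1.5 SD | Factor, shift 0.5 SD | Factor, shift 3 SD |
|---|---|---|---|
| 5% | 0.968 | 0.953 | 0.985 |
| 10% | 0.937 | 0.906 | 0.970 |
| 20% | 0.874 | 0.812 | 0.940 |
| 30% | 0.811 | 0.718 | 0.910 |

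At 20% missing the state slope is thus about 13% too small, with a range of 6% to 19% over these induction sizes. The factor multiplies the true slope, so nothing is lost if that slope is zero.

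**Simulation.** This used 12 sites, the planned total of 480 (12 × 40) or 960 (12 × 80), true slopes of −0.20 for both trait and state, 10 imputations pooled by Rubin's rules, site as fixed effects, and 500 replicates per setting. Outcomes were missing completely at random. Imputation used only the listed variables.

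| N | Missing | Trait slope | State slope | Equal slopes rejected (nominal 5%) | Trait estimate larger |
|---|---|---|---|---|---|
| 480 | 10% | −0.202 | −0.187 | 5% | 62% |
| 480 | 20% | −0.204 | −0.172 | 7% | 73% |
| 480 | 30% | −0.207 | −0.160 | 10% | 78% |
| 960 | 10% | −0.201 | −0.185 | 7% | 68% |
| 960 | 20% | −0.203 | −0.173 | 11% | 80% |
| 960 | 30% | −0.206 | −0.162 | 18% | 84% |

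With state and the post-exposure score both added, the slopes lay between −0.198 and −0.201, rejection was 4-5%, and trait was larger in 49-52% of replicates.

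**Which omission causes the tilt.** With state in the imputation model and only the post-exposure score left out, the slopes were −0.20/−0.20 under completely random dropout. When 20% dropout depended on that score, both shrank alike: −0.192/−0.192 at N = 480 and −0.195/−0.195 at N = 960. Complete case behaved the same way there (−0.192/−0.192 and −0.195/−0.194). The tilt therefore comes from omitting state.

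**Complete case.** At 20% missing completely at random it gave −0.199/−0.198, with no attenuation of state.

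**The case against.** The strongest reply is that one sentence of a journal article is being read as a full specification. The list is not said to be exhaustive, the article refers to a preregistered analysis plan that is not shown, and chained-equation routines by default use every variable in the data set. This stands as a limit: the bias arises only if the list is followed literally. It does not remove the point. The article gives an explicit list, down to condition and site, and that list omits a core predictor. Even if the pre-induction SAM rating were counted as baseline, the post-induction rating could not be.

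Second, the planned comparison with complete case could reveal the problem, because complete case is not attenuated on state. This also stands. Imputation is nevertheless the primary analysis, and a disagreement could be put down to dropout rather than to the imputation model.

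Third, the effect may be small. Follow-up is a short survey after one week, and at 5-10% missing the loss is about 3-7%. The article's Background also reports null findings for state affect, and with no state effect there is no bias. Both points are fair, and they bear on how much the issue matters here.

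**Conclusion.** The point holds in a conditional form. Followed as written, the imputation list shrinks the state slope and leaves the trait slope essentially unchanged, provided that state affect has a real effect. For a 1.5 SD induction effect the loss is about 3%, 6-7%, 13% and 19% at 5%, 10%, 20% and 30% missing. These figures rest on assumed dropout, induction size and trait–state correlation, and on an analysis model with state but without condition.

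A reader might infer three stronger things that are not supported:

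- **That both omissions favour trait.** Only omitting state does. Omitting the post-exposure ratings loses precision and leaves both imputation and complete case exposed if dropout depends on response at the visit.
- **That complete case cannot disagree with the imputed analysis.** It can differ on state, as shown. It can also differ on trait: in one scenario, with dropout driven by a baseline covariate used only in the imputation, complete case gave −0.110 against −0.104 for imputation from the listed variables (target −0.100).
- **That the trial's result will be biased.** The article does not say that the SAM ratings are excluded, and the preregistered plan may include them.

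**What to change.** State that the imputation model includes every variable of the analysis model: pre- and post-induction SAM pleasure and arousal, and any interaction tested. Add the post-exposure PRCA-PS and valence ratings as auxiliaries, alongside the baseline variables, condition and site already listed. If the preregistered plan already does this, the article needs only a sentence saying so.

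The cost is one sentence and a few lines of code, since every variable is already collected. It should be settled before the primary analysis is run. A delta-adjusted sensitivity analysis, which shifts the imputed 1-week PRCA-PS scores in steps, would be a useful option because it departs from missing at random, but this point does not depend on it.
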